### Biostatistics procedure and blinding

A biostatistician (CB) completed the computer-generated random allocation sequence for each study week and placed the sequence in sealed envelopes to be opened at the start of each week by a nurse at the NRU. NRU staff (apart from NRU nurses) and those doing screening, recruitment, enrolment, and data collection will be blinded. There are no expected reasons for un-blinding of study team members to occur. Blinding of the analysis will be performed by a biostatistician with the use of a dummy variable to code for each group. A data monitoring committee will not be necessary to analyse results un-blinded during the trial because the intervention is of very low risk. Nonetheless, an interim analysis will be completed with the internal pilot study data.

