### Trial overview and design

This study will evaluate a comprehensive structured intervention package for primary caregivers of children aged 6 to 59 months hospitalized with SAM. It will be a pragmatic trial aimed at replicating how this type of intervention could be delivered in a real nutrition rehabilitation unit (NRU) setting and its effectiveness in this setting [22]. The primary outcome is child development, which will be assessed using the Malawi Developmental Assessment Tool (MDAT), a locally adapted and validated tool for evaluating multiple domains of child development (i.e. gross motor, fine motor, language, and social domains) [23].

The design of the study is a cluster-randomized controlled trial (superiority design) that will be conducted at the Moyo NRU of the Queen Elizabeth Central Hospital in Blantyre, Malawi (NCT03072433). A cluster-randomized controlled trial design was selected because the intervention is most feasible if delivered to groups of primary caregivers rather than individual caregivers. This design will also prevent temporal overlap between the two study arms: 1) an intervention arm of primary caregivers and children with SAM participating in an intervention programme; and 2) the comparison arm of primary caregivers and children with SAM receiving standard care. All other clinical and nutritional aspects of care will be equivalent; children will be treated per hospital protocol and WHO guidelines [24]. One day of each week will be used to recruit and enrol an estimated average of four primary caregiver-child pairs. Once formed, the group will be randomly assigned to either the intervention or comparison arm. Recruitment and enrolment will not overlap with the delivery of intervention sessions, although it is possible that children from different groups will be in the NRU at the same time depending on the duration of their in-patient treatment.

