### Participant recruitment and enrolment

Children admitted to hospital with complicated SAM and their primary caregivers will be recruited at the NRU after being screened for eligibility within 3 days of admission to the NRU (*–t*
_*1*_). It is estimated based on hospital records from the NRU that there will be sufficient SAM admissions to recruit primary caregivers and children to each group.

Prior to seeking informed consent, information about benefits and risks of this study will be provided verbally and on an information sheet in Chichewa to the primary caregivers of children admitted to hospital. Written informed consent will be requested of the primary caregivers on behalf of themselves and their children (*–t*
_*1*_). For those unable to read or write, the information will be read to them in Chichewa. In these cases, informed consent by signature or thumbprint will be observed by an impartial witness.

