### Intervention: the Kusamala Program

The Kusamala Program is a 4-day counselling programme, led by NRU nurses, for primary caregivers of children with SAM in an NRU setting. Kusamala means “to take care” in Chichewa. The programme incorporates multiple modules aimed at addressing the diverse causes and consequences of SAM. The modules include:Nutrition and feeding: breastfeeding, complementary foods available in the country, safe food preparation, prevention, and early identification of malnutrition;WASH: handwashing of caregivers and children’s hands with soap after defecation and before preparing food and feeding; andPsychosocial stimulation: to promote sensitive and responsive parenting and to identify activities that the primary caregiver and child can do together, including speaking or singing, playing with toys, and looking at pictures and books.

Each of the 4 days (*t*
_*1*_
*–t*
_*4*_) of the Kusamala Program involves 45 min of counselling performed in the back bay of the NRU, which is separated from the rest of the ward by a wall. The first three sessions cover each of the three modules (i.e. one module per session), whereas the final day is a summary of all modules.

Materials for the first two modules of the Kusamala Program were based on adaptable nutrition and WASH communication and support materials from the United Nations Children's Fund (UNICEF) [27, 28]. Nutritional messages and materials for children above 2 years of age have been added since these UNICEF materials focus on infants and young children. Furthermore, there will be an additional emphasis on prevention and early identification of malnutrition.

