### Ethical considerations

NRU staff members involved in the trial, including nurses, will be taught about background information of the trial, scientific and ethical aspects of clinical research and trials, data collection tools, and communication to participants. Written consent for all participants will be taken by an enumerator after screening. All of these NRU staff members have completed Good Clinical Practice training and are fluent in Chichewa and English.

Participation in this study is completely voluntary for primary caregivers in the intervention and comparison groups. If primary caregivers are enrolled but choose to withdraw from the study at any time, they can do so without being asked to respond and without consequences. Confidentiality and respect of privacy of participants and those that withdraw will be maintained.

The Kusamala Program, which will be provided to participants in the intervention groups, is of very low risk and of potential benefit. The intervention package gives primary caregivers an opportunity to learn more about nutrition, health, and development of children. Adoption of caregiving practices requires behaviour change, which is dependent on the situation, motivation, and decisions of the primary caregivers. If primary caregivers choose to adopt recommended care practices, there may be positive outcomes for children involved in the study, other children in the household, and/or primary caregivers themselves.

Ethical approval for this study was obtained from the College of Medicine Research and Ethics Committee (P.04/16/1930) in Blantyre, Malawi, and the Research Ethics Board (1000053578) at the Hospital for Sick Children in Toronto, Canada. If any modifications are to be made to the study protocol, amendments will be submitted to both specified ethics boards and will be communicated to investigators and other study team members. It is expected that there will be no adverse events as a result of this low-risk intervention, yet if any adverse events do occur they will be recorded on a Hospital for Sick Children Adverse Event form within 48 h and will be a component of continuing review by the Hospital for Sick Children Research Ethics Board per the Tri-Council Policy Statement.

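### The allocation envelope is opened at the start of the week by an unblinded ward nurse, while the design randomises the group only once it is formed; the article does not say which comes first

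*Protocol article*

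**What the plan says.** Two sections of the protocol article describe when a group receives its allocation.

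- **Trial overview and design** gives an order of events. "One day of each week will be used to recruit and enrol an estimated average of four primary caregiver-child pairs", and then: "Once formed, the group will be randomly assigned to either the intervention or comparison arm". The same section keeps recruitment and enrolment apart from the intervention sessions.
- **Biostatistics procedure and blinding** describes the mechanics. The biostatistician "placed the sequence in sealed envelopes to be opened at the start of each week by a nurse at the NRU". Each allocation covers one week's group, because what was generated is a "computer-generated random allocation sequence for each study week".

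On who knows the arm, the latter section says: "NRU staff (apart from NRU nurses) and those doing screening, recruitment, enrolment, and data collection will be blinded". Under Ethical considerations, "Written consent for all participants will be taken by an enumerator after screening". The nurses exempted from blinding also give the intervention: "The Kusamala Program is a 4-day counselling programme, led by NRU nurses".

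**The concern.** Allocation concealment in a trial that randomises groups but enrols individuals depends on one fact: the group must be complete before anyone who could affect its membership learns the arm. The design section satisfies this. The allocation section uses a different trigger, the start of the week, and names as opener someone from the one ward group that is not blinded. No sentence ties opening to closure of the list.

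If the envelope were opened before the list closed, knowledge of the arm could affect which caregivers are approached or how willing they are to agree. The two arms could then differ in caregiver motivation or child severity from the outset. The planned ANCOVA can adjust for measured covariates but cannot be relied on to remove differences in unmeasured ones. The screening log could show an imbalance but would not prevent it.

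This is not a detail left to a fuller document. The article states a rule for opening the envelopes, and that rule does not fit the sequence it gives elsewhere.

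**Working it through.** The check compares statements; the plan gives no figure on this point to reproduce.

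**1. Trigger for disclosure.** Design section: completion of the group. Allocation section: start of the week. These coincide only if the group is already complete when the week starts, or if the start of the week is read loosely as the end of the recruitment day. The article states neither.

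**2. Possible schedules.** The recruitment day is not fixed within the week.

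- Recruit late in one week and open at the start of the next: both sections are satisfied.
- Recruit on the first day and open after the list is closed: both are satisfied on a loose reading.
- Recruit on the first day and open that morning: the arm is known before the first consent.
- Recruit in mid-week and open at the start of that same week: the arm is known before recruitment.

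Two of the four are sound and two are not. The allocation wording allows all four.

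**3. What the timetable suggests.** One recruitment day plus four programme days makes five days (1 + 4 = 5). If a study week is a five-day working week that holds both (an assumption), recruitment falls on the first day, when the envelope is also opened. The recruitment start under Trial status, 28 November 2016, was a Monday, which fits. However, recruiting on the last working day and running the programme on the first four days of the next week uses the same five days and is sound. The timetable does not settle the matter.

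**4. Who could act on early knowledge.** Foreknowledge is documented only for nurses. Recruiters and enrollers are stated to be blinded, and consent is taken by an enumerator. Nurses are not given a role in screening, approach or consent. Two routes to bias remain:

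- *Leakage to enumerators.* Both work on the same ward. Under Data collection and management, assessments may take place in the back bay, which is also where the programme is delivered.
- *Direct influence on caregivers*, from ward staff who already know the arm.

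**5. Room for discretion.** Consent is voluntary, and one exclusion (expected death within 6 months) rests on the treating physician's opinion. Children are "screened for eligibility within 3 days of admission to the NRU", so the pool changes from week to week. The Abstract caps groups at six and the design section expects four on average, so choosing among a surplus of eligible pairs may seldom arise.

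**6. How often it recurs.** With 320 pairs and four per group, 320/4 = 80 groups. If every group were full at six, 320/6 = 53.3, so at least 54.

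**7. Size of any bias.** The document gives no enrolment proportions by arm and nothing on how enrolled and non-enrolled children differ. Any shift in the treatment difference would have to be invented, so no error rate is given.

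**The case against.** The strongest reply is that the article already has the right order and the right people. The design section puts group formation before randomisation. The allocation section may be read as saying mainly who generates and opens the sequence, with a study week that begins once the group exists. Recruiters are blinded, an enumerator takes consent, groups are expected to run below capacity, and the screening log under Statistical analysis records eligible, excluded and recruited participants.

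Much of this stands. The benign reading is possible, the separation of recruiters from nurses is a real safeguard, and the screening log already provides most of what is needed to look for differential enrolment. It does not remove the point, for two reasons. The benign reading is nowhere stated, and a nurse following the allocation section to the letter could open the envelope before anyone has consented. Also, if the envelope is opened early, recruiter blinding depends on nurses not revealing what they know; if it is opened after the list is closed, enrolment is protected whatever they know.

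A reader might go further and infer that nurses see every eligible caregiver and decide whom to put forward. The article does not say so. It describes them delivering sessions, supervising play and counselling at discharge.

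**Conclusion.** The two sections do not agree on what triggers disclosure, and the allocation section, taken literally, permits the arm to be known on the ward before that week's group is complete. That much rests on the wording alone.

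A reader might infer that concealment failed, or that caregivers were recruited after randomisation. The document does not support this: the design section states the opposite order, and at least one ordinary weekly schedule satisfies both sections. Nor can a bias or an inflated false-positive rate be attached to the point, because any assumed shift would be arbitrary in size and direction.

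The point bears on the primary comparison and recurs across roughly 54 to 80 groups, depending on group size. Its practical weight depends on two things the article does not report: when envelopes were actually opened, and whether nurses had any contact with caregivers about joining the study. If practice followed the design section, only a sentence needs correcting. If it followed the allocation section literally, concealment rested on nurses keeping the arm to themselves.

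**What to change.** Reconcile the two sections with a single rule:

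- Each group's envelope is opened only after the enumerator has closed the list of consented pairs and completed their enrolment assessments.
- The date and time of opening are recorded.
- No pair is added to a group after opening.
- Whoever opens the envelope has no part in screening, approach or consent.

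Apply the rule to all remaining groups. Recruitment began on 28 November 2016 and the article appeared on 17 November 2017, so nearly a year of groups may already have been allocated. State in the trial report what was done for those. From the existing screening log, compare enrolled/eligible by arm.

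The cost is negligible: one sentence, a closed list, and opening moved to the end of the recruitment day. It changes no sample size, intervention or outcome. Its limit is that groups already allocated cannot be corrected, only described.

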### Data collection and management

Data collection will be performed by three different enumerators who have been trained on all relevant assessment tools and questionnaires, including the MDAT. Baseline data collection will take place over approximately 80-week-long cycles, depending on enrolment rates, with assessments performed at enrolment (–*t*
_*1*_) and at discharge (*t*
_*5*_). These data collections will be done privately in the NRU, either in the procedures room or in the back bay depending on availability of these locations. Home visits will be conducted for follow-up assessments 6 months after children are discharged from hospital (*t*
_*6*_) over the course of 80 weeks. For participants who prefer not to be visited in the home, they will be asked to come back to the NRU for follow-up assessments.

Investigators will maintain medical and research records for this trial in compliance with regulatory and institutional requirements for the protection of confidentiality of subjects. All personnel with access to data and information related to this trial will take all reasonable precautions to maintain the confidentiality of information. Data will be collected using paper forms which will be kept in a locked filing cabinet and will be accessed only by the investigators. Data entry will be performed into a Research Electronic Data Capture database, which includes automated checks for data values with coded numbers [41]. De-identified data will be exported in a password-encrypted file.

### Statistical analysis

Bias will be determined by maintaining a screening log of all potentially eligible participants and those who were excluded or recruited to the two arms. This will be presented as a flow diagram in the final report according to the Consolidated Standards of Reporting Trials (CONSORT) guidelines (Fig. 2) [42].

**Fig. 2 Fig2:**
[figure not shown]
Modified version of the CONSORT 2010 flow diagram

Data will be analysed using the statistical software Stata 14, R v3.2.5, and WHO Anthro v3.2.2 for anthropometric *z*-score calculations [43–45]. Missing data will be accounted for depending on the nature of drop-outs and loss to follow-up.

Descriptive statistics will be performed to summarize baseline characteristics of participants in both the intervention and comparison groups. More specifically, means and SD will be calculated for continuous variables such as the age of children, whereas the number of participants and percentages will be calculated for categorical variables such as the presence of oedema.

MDAT *z* scores standardized by age and based on a reference population of Malawian children will be calculated [23]. *Z* scores of each domain will be analysed separately to understand if the intervention influences certain domains more than others and a composite score of overall child development will be calculated if statistically appropriate. Upon completion of data collection for the internal pilot study, the variance of the primary outcome, child development using the MDAT, will be determined. The variance will be used to recalculate the sample size for the full trial [25, 26].

To determine the effect of the intervention on the primary outcome measures and continuous secondary outcomes, analysis of co-variance (ANCOVA) will be conducted to determine if there are differences between the intervention groups and the comparison groups while allowing for adjustment of co-variates in the analysis [46].

Multiple logistical regression will be performed to determine whether the intervention influenced binary outcomes such as the presence or absence of oedema. Subgroup analyses will be performed with participant age categories (i.e. infants and older children) and types of SAM (i.e. marasmus and kwashiorkor), and neurodisability, since children with neurodisability such as cerebral palsy are included in this study.

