### Primary outcome

The primary outcome is child development 6 months after discharge (*t*
_*6*_). Child development will be assessed with the MDAT. The MDAT has been evaluated in 1426 healthy Malawian children as well as children with neurodisability (*n* = 80) or with severe wasting (*n* = 120) [23]. In this evaluation, sensitivity was 97%, and 18% of healthy children failed, translating to specificity of 82% [23]. These results show that the MDAT is an appropriate tool for assessing child development in Malawi.

The MDAT will be used at discharge (*t*
_*5*_) and 6 months later (*t*
_*6*_) to examine development in four domains: gross motor, fine motor, language, and social development [23]. Children will be given a pass or fail depending on their ability to complete increasingly advanced items on the MDAT [23]. The sum of passed items can be calculated and translated to age-specific *z* scores based on healthy Malawian children as reference standards [23].

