### Sample size calculation

The sample size estimate is based on cross-sectional study data of development of children with SAM at discharge from the NRU using the MDAT [38]. Results from this study showed that, based on MDAT *z* scores, the variance for gross motor was 1.9 SD, for fine motor was 1.2 SD, and for language was 1.7 SD [38]. Therefore, the composite variance for those domains was 1.6 SD. This was used to calculate the sample size using α = 0.05 and 80% power, an estimated intracluster correlation coefficient of 0.001, and with an expected effect size of 0.5 using Cohen’s *d* [39, 40]. With this approach, the initial estimate of the sample size for the primary outcome is a minimum of 160 primary caregiver-child pairs per arm (*n* = 320). As discussed previously, an internal pilot study will be conducted to determine the variance of the primary outcome in the first 15 children in each study group at 6 months post-discharge from hospital which will be used to recalculate the sample size [25].

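### The plan asks whether the programme affects some MDAT domains more than others, but the only analysis it names tests each domain against no effect, not the domains against each other

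*Protocol article*

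**What the plan says.** The Primary outcome section uses the MDAT "to examine development in four domains: gross motor, fine motor, language, and social development". Under Statistical analysis, the plan for the domain results reads: "scores of each domain will be analysed separately to understand if the intervention influences certain domains more than others". An overall measure is planned only conditionally, in these terms: "a composite score of overall child development will be calculated if statistically appropriate". The method for the primary outcome measures, and for secondary outcomes that are continuous, is given with covariate adjustment as follows: "analysis of co-variance (ANCOVA) will be conducted to determine if there are differences between the intervention groups and the comparison groups". The section names no arm-by-domain term, multivariate model or contrast between domain effects. The conditional composite addresses overall development, not differences between domains.

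The Sample size calculation section supplies the spread: "the variance for gross motor was 1.9 SD, for fine motor was 1.2 SD, and for language was 1.7 SD". It gives no figure for the social domain.

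**The concern.** Asking whether one domain is influenced more than another is a question about differences between effects, and its null hypothesis is that the effect is the same in every domain. A separate ANCOVA in each domain has a different null: no arm difference in that domain. One domain can be significant and another not while the two effects are identical, because each estimate carries its own sampling error and, here, its own spread.

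The article states both the purpose and the method, and the method does not serve the purpose. That is more than a detail left out of a condensed text, since an analysis plan that followed the sentence faithfully would inherit the mismatch.

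What is at stake is a false report that the programme works in some developmental domains and not in others. A stricter per-domain alpha would not cure this, because each test would still have the same null.

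**Working it through.** **Inputs from the protocol article.** 160 per arm, alpha 0.05, 80% power, effect size 0.5, intracluster correlation 0.001 and composite SD 1.6 (Sample size calculation). Domain SDs are 1.9 (gross motor), 1.2 (fine motor) and 1.7 (language), from the same section; the text calls them variances but gives them in SD units. Average group size is 4 (Trial overview and design).

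**Assumptions, not in the article.** Between-domain correlation 0.3 to 0.9; social-domain SD 1.6; normally distributed estimates; no covariate adjustment.

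**Step 1. Reproduce the stated sample size.** n per arm = 2(1.960 + 0.842)² × SD² / difference² = 2 × 7.849 × 1.6² / 0.5² = 160.7. The design effect 1 + (4 − 1) × 0.001 = 1.003 gives 161.2, against 160 stated. So the figure corresponds to a gain of 0.5 in z units with SD 1.6, a standardised effect of 0.5 / 1.6 = 0.31. A standardised effect of 0.5 would need 2 × 7.849 / 0.25 = 62.8, or 63 per arm.

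**Step 2. Per-domain power for the same 0.5 z gain.** SE = SD × √(2/160); power from the two-sided t test.

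| Domain | SD | SE | 0.5 / SE | Power |
|---|---|---|---|---|
| Gross motor | 1.9 | 0.212 | 2.35 | 65% |
| Fine motor | 1.2 | 0.134 | 3.73 | 96% |
| Language | 1.7 | 0.190 | 2.63 | 75% |
| SD 1.6 (composite; assumed for social) | 1.6 | 0.179 | 2.80 | 80% |

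**Step 3. How often equal effects give a mixed pattern.** I drew 400,000 sets of correlated domain estimates with a true gain of 0.5 z in every domain and 160 per arm. A mixed pattern means at least one domain with p < 0.05 and at least one without.

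| Correlation | Three domains, stated SDs | Four domains, social SD 1.6 | Four domains, SD 1.6 throughout |
|---|---|---|---|
| 0.3 | 47% | 54% | 49% |
| 0.5 | 43% | 48% | 41% |
| 0.7 | 38% | 42% | 32% |
| 0.9 | 33% | 34% | 18% |

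A Wald test of equal effects across domains rejected in 5% of trials in every cell. The last column shows that unequal SDs are not needed for the problem to arise.

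**Step 4. Dependence on the true effect** (four domains, correlation 0.3-0.9).

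- Equal gain of 0.4 z, stated SDs with social 1.6: 43-73%.
- Equal gain of 0.7 z: 10-14% with those SDs and 4-9% with SD 1.6 throughout, so 4-14% overall.
- True standardised effect of 0.5 in every domain: about 2% at most.

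**The case against.** The strongest objection is that the article contains no rule saying domain differences will be read from p-values. Separate ANCOVAs also give an effect estimate per domain, all in z units from one Malawian reference population, and these can be set side by side. The sentence may only be explaining why domains are reported as well as a composite, and a between-domain model is the sort of detail an analysis plan supplies. The first part of this stands. A reader might infer that the trial will often report domain-specific effects that do not exist, but the text does not support so firm a prediction. It supports only that no valid basis for the comparison is named. The appeal to the analysis plan stands less well, because the article itself ties the purpose to the separate analyses.

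A second objection also stands: equality depends on the scale. A common 0.5 z gain is 0.5 / 1.2 = 0.42 SD in fine motor and 0.5 / 1.9 = 0.26 SD in gross motor, so effects equal in z units are unequal once standardised. A remedy that names no scale would leave the question open.

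Third, the percentages rest on correlations and a social-domain SD that the article does not give. The SDs come from cross-sectional data at discharge, not from the 6-month endpoint. The sample size is to be recalculated from the internal pilot. The size calculation also refers to Cohen's d, and a literal standardised effect of 0.5 would make mixed patterns rare, although that reading gives 63 per arm and not 160.

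Finally, a reader might infer that a false domain finding would misdirect revision of the psychosocial module. The Discussion and Conclusion speak of adapting the programme to other settings, not of revising a module by domain. Comparing domains is also not among the stated objectives.

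**Conclusion.** The point holds as a mismatch between a stated question and the stated method. If the comparison between domains is read from which domains are significant, equal effects of 0.5 z produce a mixed pattern in roughly 18-54% of trials at 160 per arm, against 5% for a direct test of equality. That range assumes a between-domain correlation of 0.3-0.9 and either the stated SDs with social at 1.6, or 1.6 throughout. It counts splits in significance, not published misstatements, and it depends strongly on the true effect: higher at 0.4 z with the stated SDs, about 4-14% at 0.7 z. The per-domain and overall comparisons between arms remain valid. Only the claim that effects differ between domains lacks a test.

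**What to change.** Keep the per-domain estimates with confidence intervals. Add to the analysis section that any statement that effects differ between domains will rest on the arm-by-domain test, and on between-domain contrasts with intervals, from one joint model of each child's domain z scores. That model would include domain, arm and arm-by-domain terms, domain-specific variances, an unstructured within-child covariance and the weekly group. State in advance whether effects are compared in reference z units or standardised by domain SD. State also that differences in significance between domains will not be read as differences in effect. If the investigators prefer not to add this, the comparative purpose should be dropped from the sentence.

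The cost is one further model on data already being collected and a few lines of text. The drawback is limited power for small between-domain differences, so fewer domain-specific claims will be possible.
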